**Figure 1 F1:**
[figure not shown]
**
*The Academy for Future Science Faculty *
****trial design.**

One of the most critical decisions in designing the *Academy* was whether to include students of all races/ethnicities, or to focus just on URM students. On one hand, it could be argued that an *Academy* for only URM students would concentrate efforts on students who might need these resources most, rather than non-URM students who are more likely to have the resources they need to succeed in the biomedical sciences. However, diversity efforts targeting URM students alone can create a significant stigmatizing effect on those who participate (e.g. [33]). There is also great value in exposing non-URM students to some of the issues and barriers faced by their URM peers as they are discussed in the *Academy* meetings and in the individual coaching groups. Our model also provides opportunities for non-URM students to share inside knowledge that they have gained with their URM peers who may have not yet acquired that knowledge. Finally, the inclusion of both URM and non-URM students was essential in order to determine if the *Academy* differentially could impact URM students vs. all biomedical science PhD students. Therefore, an equal number of men and women were chosen, and equal numbers by race and ethnicity. Thus, for *Academy I*, there are 24 each of Caucasian, Asian, Hispanic and African American students. Only 4 Native American students applied to Academy I, so they were all assigned to the Academy rather than controls as it would not be a meaningful comparison between just 2 students. In *Academy II*, there are 15 each of Hispanic and African American students, 14 each of Asian and Caucasian students, 1 Native American student, and 1 Pacific Islander student. Students in both *Academies* were then assigned to Coaching Groups of 10 students and 1 Coach. These groups were also randomly assigned but stratified such that each group had the maximum diversity possible by gender, race and ethnicity.

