### Student recruitment

On April 10, 2011, an email describing the *Academy* was sent to biomedical graduate school leaders who were members of the GREAT group, graduate directors at other non-medical major research training universities, and leaders of undergraduate diversity STEM programs throughout the U.S. This date was chosen because it was just before the April 15 common deadline for students to make the final decision of where to pursue their PhDs among the offers of acceptance they had received. Those receiving the emails were asked to forward it to incoming PhD students, or undergraduates they had advised who were starting the PhD in fall 2011. It was advertised as multi-year professional development program particularly designed for those with a strong interest in a future academic career. It was made clear from the start that it was a randomized controlled trial of the program; applicants would not be reviewed, ranked or chosen based on credentials or prior experience. Three hundred and fifty students applied for the *Academy*, representing a wide variety of PhD programs in the U.S. From this applicant pool, 100 students were selected to participate in the *Academy*, and 104 students were selected as study controls who received no intervention. The 204 total students recruited for *Academy I* represents the maximum number of students that could be supported under our funding. Eligibility to participate in the *Academy* required: 1) an expressed interest in an academic career in science; 2) U.S. citizenship or permanent residency; and 3) first year PhD student status.

In April, 2012, a similar email was sent to the leaders of biomedical PhD training programs describing the second round of the *Academy II*, but this time asking them to forward it to all PhD students who were within 12–18 months of completing their degrees. Approximately 340 applications were received and were stratified and randomized. For this study, 60 were chosen for *Academy II*, and 61 were chosen for controls (to account for anticipated dropouts of the study) (Figure 1). As we anticipated more drop-offs from beginning PhD students compared to those finishing the PhD, the *Academy II* group is smaller than the *Academy I* group.

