### Quantitative methods and analysis

We collected quantitative data in the forms of yearly pre-interview surveys and yearly evaluations for the *Academy* in-person meetings. Quantitative data will be analyzed using SPSS version 21 [34]. We will utilize a variety of analyses of variances to determine difference between our sample populations of interest (e.g. control vs. experimental, men vs. women, URM vs. non-URM).

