## Endnotes

^a^In our research, we define underrepresented minority groups as those that have been underrepresented in the biomedical sciences – specifically African-Americans, Hispanics, and Native Americans. Asian-American students were considered non-URMs, along with white students, because they are numerically well-represented in science vis-à-vis African-American, Hispanic and Native American students.

^b^Citing Bourdieu, the authors define habitus as “a system of class specific dispositions that shape an individual’s actions so as to reproduce and perpetuate existing systems of hierarchy” (p. 373).

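### In Academy I the four Native American students were placed in the intervention by decision, yet nothing sets them aside from the randomised arm and URM comparisons

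*Protocol article*

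**What the plan says.** The protocol article presents the study as a randomised trial. Under Student recruitment it tells the reader that "It was made clear from the start that it was a randomized controlled trial of the program". For Academy I it reports that "100 students were selected to participate in the" Academy and that "104 students were selected as study controls who received no intervention", which gives the total of 204.

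Later in the same section, after Figure 1, the experimental group is broken down as 24 students in each of four racial or ethnic groups, followed by an exception: "Only 4 Native American students applied to Academy I, so they were all assigned to the Academy rather than controls". The reason offered is that a comparison based on two students would not be meaningful.

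Endnote a defines the URM groups as "specifically African-Americans, Hispanics, and Native Americans". The Analyses section sets out the hypothesis: experimental students will be more likely to pursue an academic career, and URM and non-URM proportions will become more equal. Quantitative methods and analysis then gives, as examples of the contrasts to be tested by analysis of variance, "control vs. experimental, men vs. women, URM vs. non-URM". None of these sections says how the four students are to be handled.

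**The concern.** A comparison of randomised arms is protected from confounding because every student in it could have ended up in either arm. That is not true of these four. If they stay in the experimental arm, the contrast mixes a randomised comparison with a small non-randomised addition on one side only.

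The addition falls in the URM group, and the article says both URM and non-URM students were included so that a differential effect on URM students could be examined. Within Academy I, being Native American and being in the experimental arm coincide completely. A race term in the model therefore has no Native American controls from which to estimate the arm difference.

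The stated reason does not answer this. Two against two is indeed too few for a Native American subgroup result. But four students randomised within their stratum could still have contributed validly to the pooled arm and URM comparisons. The small number argues against a subgroup analysis and gives no ground for counting non-randomised students in the pooled ones.

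**Working it through.** **Inputs from the article.** Academy I experimental 100, control 104, total 204; 24 experimental students in each of the Caucasian, Asian, Hispanic and African American groups; 4 Native American students, all experimental; URM = African American, Hispanic and Native American.

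**Reproducing the article's count.** 4 × 24 + 4 = 100, and 100 + 104 = 204. The stated 100 is reached only if the four are included. Without them the comparison is 96 vs 104.

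**Share of the affected groups.**
- Academy I experimental arm: 4/100 = 4.0%.
- Academy I experimental URM students: 24 + 24 + 4 = 52, so 4/52 = 7.7%.
- Academy I controls: 0, because all four applicants went to the Academy.
- Both Academies pooled: 4/(100 + 60) = 2.5% of experimental students. Academy II has 15 + 15 + 1 = 31 experimental URM students, so 4/(52 + 31) = 4/83 = 4.8% of experimental URM students.

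**Shift caused by including them.** Shift = (4/n) × (rate in the four − rate in the other students of that group). The article gives no outcome rates, so the differences below are assumptions.

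| Assumed difference | Whole arm (n = 100) | URM students (n = 52) |
|---|---|---|
| 30 points | 0.040 × 30 = 1.2 points | 0.077 × 30 = 2.3 points |
| 50 points | 0.040 × 50 = 2.0 points | (4/52) × 50 = 3.8 points |

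**Outer limits.** Suppose the other students' rate lies between 10% and 50% and the four all fail or all succeed. The arm rate then shifts by −2.0 to +3.6 points and the URM rate by −3.8 to +6.9 points. For example, at 10% with all four succeeding, the URM shift is (4/52) × 90 = 6.9. On a continuous score, a 1 SD difference moves the arm mean by 0.04 SD and the URM mean by 0.077 SD.

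**Scale against sampling error.** Assume about 52 URM students per arm and a 30% rate (neither the control make-up nor the rate is in the article). The standard error of the URM arm difference is √(2 × 0.30 × 0.70 / 52) = 0.090, or about 9 points. A shift of 2.3 to 3.8 points is then roughly 0.26 to 0.43 of a standard error.

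**The case against.** The strongest reply is that the article does not commit itself to pooling these students. It introduces its contrasts only as examples and defines no analysis set; a separate analysis plan could exclude the four. This stands to a degree: a reader might infer a firm plan to analyse all 100 as randomised, and the text does not go that far. But the allocation itself is a stated decision, the four are counted in the arm and in the URM definition, and following the article as written would include them.

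A second reply is that the exception is disclosed. That is correct. A reader might infer that the article falsely describes these four as randomised. It does not: it says openly where they were placed and why, and the abstract claims balance by race and ethnicity only as far as was possible. What is lacking is a link between the general description of the trial as randomised and this exception.

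A reader might also extend the point to Academy II, where the Academy group includes "1 Native American student, and 1 Pacific Islander student". The documents do not support that. Student recruitment says the Academy II applications were stratified and randomised, and the article gives the make-up of the controls for no racial or ethnic group in either cohort. The absence of a described counterpart is therefore no evidence of non-random placement. Pacific Islanders are also not among the groups named in the URM definition.

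Finally, the effect is small, and the four are identifiable and can be removed at analysis. Both statements hold. They limit the severity, and they also make the correction easy.

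**Conclusion.** The point holds for Academy I, with modest severity. Four students with no chance of being controls are counted in the experimental arm and in its URM group, nothing shown sets them aside, and the stated reason does not justify their place in the pooled comparisons.

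The direction of any bias is unknown, and its size rests on assumed differences in outcome. Even under the large differences assumed, it stays well below one standard error of the URM contrast. A reader might be tempted to conclude that the trial's arm comparison is invalid. The figures do not support that: the other 96 experimental students can be compared with the controls without the four. Still, the bias is avoidable, is proportionally larger in the URM group, and cannot be removed by covariate adjustment.

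**What to change.** Define the Academy I arm comparison as the 96 experimental students outside this exception versus the 104 controls, with 48 rather than 52 experimental students in the URM contrast. Report the four Native American students descriptively, and give the analysis of all participants as a sensitivity analysis. Where the trial is described as randomised, add a sentence noting that these four were assigned directly. The report should also say that the randomised URM contrast in Academy I then speaks for African American and Hispanic students only.

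The cost is 4% of one arm. For illustration, with an assumed difference of 0.4 SD and two-sided alpha of 0.05 (neither is in the article), power goes from 81.5% with 100 vs 104 to 80.7% with 96 vs 104. Only the analysis set and the description change; the four students' participation in the Academy is unaffected.

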### Study design

The *Academy* activities are designed to consciously promote success and advancement while keeping in mind the theory-derived extra challenges URM students can face. For example, the precision and accuracy with which beginning PhD students know what to expect and how to excel in the first PhD year (e.g. cultural capital) is highly variable. Students with less prior research, from less research-intensive universities, and from lower SES backgrounds often can face greater challenges. URM students often face additional identity concerns around fitting in, belonging, finding others like themselves, and the heightened sense of everyone watching their performance. Activities at the *Academy* meetings were designed to bring everyone up to a high understanding of what to expect, acknowledge concerns about fitting in, and assist students to develop strategies for success.

A major focus for both Coaches and the research/program design team was to begin building a CoP among the larger group and individual coaching groups, so they could draw on the collective group expertise and knowledge. Reinforcing the idea that going into research is something that can be consciously and strategically planned and structured, we emphasized that becoming successful as scientists is a learned skill. Through the modeling of a creative and safe environment, another objective and focus of the *Academy* meetings was to encourage students to discuss issues of identity and diversity in science. Students explored their important primary identities, acquired insights into the importance and realities of developing and maintaining identities beyond the scientific identity of a graduate student, and were able to find others within the *Academy* community with whom they shared similar interests and identities. Further, by making the *implicit* process of what students could expect from mentors and PIs more *explicit*, students gained useful cultural capital in the form of insider knowledge about how biomedical science graduate programs function and operate.

One truly unique aspect of the *Academies* was the introduction of the three social science theories through short (15–30 minutes) lectures and discussions of each, showing how the theories translated to practices within the research community. By learning about the underlying, often invisible, social processes within research groups, students (and Coaches) could become more adept at navigating the process of scientific development, ideally preparing them to better fit in within the graduate program and research group CoPs. The *Academy* was therefore developed as a means to create a community of both students who have an expressed desire for a future academic career and successful scientists/professionals with a deep understanding of what is required to achieve and excel in such a career. The *Academy* was designed to encourage a supportive and cohesive community, both within the coaching groups and through the *Academy* as a whole.

### Academy meetings

During the time of the *Academy* funded by the ARRA grant (September, 2010-August, 2013) the *Academy I* meetings consist of a 72 hour in-person meeting in July, 2011 in the Chicago area. Subsequent meetings of both groups lasted 48 hours were held over 3 days. For the meetings in 2012 and 2013, the meeting design included 1 day of overlap between *Academy I* and *II* to allow programming of value to both at the same time plus interactions between the early stage and later stage students. About half of the time at each meeting was devoted for full-group activities and half to Coaching Group time. During these meetings, students were provided with guidance relevant to their upcoming year and stage in graduate school. Every year, students were reminded of the social science theories to help them understand some of the invisible social processes that can affect scientific development. Coaches also reinforced the theories with their groups. The actual topics covered during each meeting were chosen to cover the most critical information and perspectives for the upcoming year, plus longer vision information. For example, in the first *Academy I* meeting, much time was spent on what to expect in the first year of the PhD and how to excel, but a detailed introduction to the road to an academic position was provided. The purpose was to not only facilitate success in the first year but provide a concrete vision of how on achieves an academic career. Equally important in the research design is the introduction of Coaches which is why equal time was spent in full-groups and coaching groups. Time was also scheduled at each meeting for one-to-one meetings between each student and his or her Coach. See Additional file 2 for a sample meeting agenda for *Academy I*, and Additional file 3 for a sample meeting agenda for *Academy II*.

One very unique and novel aspect of the *Academy* meetings was the design and testing of ways to open up meaningful conversations among students and Coaches around issues of privilege, race, bias, and the real-life issues about being ‘different’. This was done subtly during the first 2011 meeting as it was unclear what kind of community would be created when everyone came together. The larger *Academy* community and the Coaching Groups bonded even faster and more strongly than we expected which made it possible to experiment with providing more explicit presentations to create conversations in 2012 and 2013. Those conversations were initiated in 2012 by bringing in an expert in critical race theories and the ongoing influences of racism in America to address the groups and start the conversations. In 2013, a different speaker was brought in to address the psychological and physiological stresses associated with isolation and being ‘the only one,’ and strategies to deal with those stressors. In both cases, the very open, honest, and deep conversations started by these presentations continued on in subsequent Coaching Group discussions and throughout the remainder of each meeting.

### Activities of coaching and coaching groups between Academy in-person meetings

A core element of the *Academy* trial is the ongoing coaching and relationships between the yearly meetings. The need for and value of a Coach is ongoing, although by no means continuous. The *Academy* experiment is providing a variety of tools and approaches to keeping students and Coaches connected throughout the year. This part of the Academy is also experimental as Coaches and students are provided with several options to use as they prefer. The initial design called for Coaching Groups to have monthly or bi-monthly virtual meetings (video and audio) using a product called Adobe Connect. Over time, some groups have migrated to other virtual meeting platforms, some have stopped meeting formally, and others have adopted alternative ways of keeping in touch. Coaches check in with their students on a regular basis via email or phone as well, and students often contact each other independently. Thus, by not rigidly scripting group behavior, each group has been allowed to organically evolve and we are able to gather data on many different variations. A few webinars around specific topics were also delivered to determine how many individuals would find that mode of information delivery of interests.

The initial funding for the *Academy* trial ran out in August, 2013, but a second grant was obtained from NIH to continue some aspects of the study. The new grant enables support of the Coaches and their groups in their virtual meetings, our delivery of new material and experimenting with other ways to provide content, but does not have sufficient funding to enable the annual meeting. However, based on feedback from the last full meetings in 2013, there was a very strong desire to keep meeting in some way. As a result, we have found alternative funding to enable individual Coaching groups to meet, and a majority of them are making plans to do so in the summer of 2014. The new grant also supports the continuation of logistical support for the Coaching Groups, and full collection of data to study how they function, and the comparison between the *Academy* students and the Control. The Coaches, on their own from day one, made it clear to their students that they would be available to them for as long as they desired irrespective of external funding for the *Academy* study.

### Analyses

The primary intention of our intervention is to continue supporting interactions between Coaches and their groups, and follow students longitudinally to see if the *Academy* makes a tangible difference in long-term career choices. The hypothesis is that experimental students will have a higher likelihood of pursuing an academic career after the PhD, and that the proportion of URM and non-URM students will be more equal than the past extremely low rate for URM students. These dynamics will be measured through annual interviews with students and quantitative responses on their perceptions of the achievability, desirability, and their commitment to an academic career throughout graduate school and subsequent career steps. These career steps, such as arranging post-doctoral positions that will likely lead to a successful academic career, will provide interim measures.

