## Background

From any perspective other than diversity, the United States has been very successful at developing a talented and creative community of biomedical scientists. However, previous approaches to training have failed to produce satisfactory improvement in the participation of women and individuals from underrepresented minority groups (URMs)^a^, especially beyond the early stages of training. Over the past several decades, the fraction of URMs in faculty and leadership positions has changed little [1,2]. According to the 2010 Census, URMs make up approximately 30% of the U.S. population. However, individuals from these groups only make up approximately 9% of Science, Technology, Engineering and Math (STEM) PhD recipients [3]; National Academy of Sciences, National Academy of Engineering, Institute of Medicine, [4]. Furthermore, only 4% of faculty in basic science departments of U.S. medical schools and biological science departments at the top 50 colleges and universities are URM faculty – a number that has changed little in several decades [1]. This lack of improvement, despite vast infusions of money and the time and energy of many dedicated people, suggests that these efforts are either trying to fix the wrong problem or using the wrong methods to address the problems [3-6]. This lack of diversity in the faculty ranks is the central problem our study is attempting to change. However, we are starting from the time of PhD as the vision and trajectories toward an academic career are critically set during early research training.

Most of the efforts to increase diversity have focused on getting a more diverse pool of young scientists up to the starting line of the PhD (e.g. [7]). These approaches are pursued with the assumption that standard training practices will propel more of them to higher levels of success. However, these standard practices often overlook the very strong social and psychological processes that mediate not only development but perceptions of ability and talent.

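### The URM part of the hypothesis is set against a historical rate that the selected sample could well beat with no Academy effect; it should be set against the concurrent control arm

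*Protocol article*

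**What the plan says.** The Analyses section of the protocol article gives one hypothesis in two parts. The first is: "The hypothesis is that experimental students will have a higher likelihood of pursuing an academic career after the PhD". The second concerns diversity: "the proportion of URM and non-URM students will be more equal than the past extremely low rate for URM students". The second part names the past as its comparator and does not mention the control arm.

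The Background supplies the only historical URM figures. For doctorates it says that "individuals from these groups only make up approximately 9% of Science, Technology, Engineering and Math (STEM) PhD recipients". For faculty it gives "only 4% of faculty in basic science departments of U.S. medical schools" and of biological science departments at leading universities.

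The Student recruitment section describes how the sample was formed. Eligibility required "an expressed interest in an academic career in science", and "an equal number of men and women were chosen, and equal numbers by race and ethnicity". It reports 104 concurrent controls for Academy I and 61 for Academy II. The text after Figure 1 explains that both URM and non-URM students were needed "in order to determine if the" Academy affects URM students differently from PhD students at large.

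The Quantitative methods and analysis section plans analyses of variance between populations of interest, with the examples "control vs. experimental, men vs. women, URM vs. non-URM".

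**The concern.** A historical benchmark is informative only if the trial sample resembles the population behind it. Here two features separate them before any coaching takes place. The race composition was fixed by design at about half URM, and every student had declared an interest in the outcome being measured. Either could make the Academy group look more equal than the past.

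A success against that benchmark would therefore not show an Academy effect, and the trial could announce a diversity benefit that its own controls do not support. The benchmark also leaves open the question that the article gives as its reason for enrolling both groups, namely whether the Academy works differently for URM students. That needs the URM/non-URM gap in one arm set against the gap in the other. Finally, a more equal proportion can come from a fall among non-URM students as well as from a rise among URM students.

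**Working it through.** **Figures in the plan.** The article states no power, effect size or event rate, so there is no power calculation to reproduce. The counts add up: Academy I, 4 × 24 + 4 = 100, and 100 + 104 = 204; Academy II, 15 + 15 + 14 + 14 + 1 + 1 = 60.

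**URM share of the Academy arms.** The article's first endnote defines URM as African-American, Hispanic and Native American. Academy I: 24 + 24 + 4 = 52 of 100. Academy II: 15 + 15 + 1 = 31 of 60. Together: 83 of 160 (52%), with 77 non-URM.

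**Illustrative historical relative rate.** From the Background shares, r = (4/96) / (9/91) = 0.42. This divides faculty in certain departments by recipients of all STEM doctorates, so it is an illustration and not a measured transition rate.

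**Reading 1: the proportion is the URM share of those continuing.** With no Academy effect, share = 83r / (83r + 77).
- r = 1: 83/160 = 52%.
- r = 0.42: 34.9/111.9 = 31%.
- r = 0.25: 20.75/97.75 = 21%.
- For the share to fall to 4%, r must be (0.04/0.96) × (77/83) = 0.039. For 9%, r must be (0.09/0.91) × (77/83) = 0.092.

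Exact binomial chance of significantly exceeding the benchmark in Academy I (one-sided 0.025), with no effect, assuming non-URM entry rates of 30% to 50% and r from 0.42 to 1: 93% to 100% against 4%, and 68% to 100% against 9%.

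**Reading 2: within-group rates.** The URM:non-URM rate ratio is compared with 0.42, taken as known. Simulation with no Academy effect, Academy I alone and both cohorts pooled, non-URM entry rate 30% or 50%:

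| Ratio in the sample after selection | Point estimate beats 0.42 | Significantly beats 0.42 |
|---|---|---|
| 0.42 (no narrowing) | about 49% | about 3% |
| 0.6 | 82–95% | 18–42% |
| 0.8 | 96–99.9% | 50–94% |
| 1.0 | 99.5–100% | 80–99.9% |

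**Contrast against the concurrent controls.** The difference in differences is d = (URM − non-URM, Academy) − (URM − non-URM, control), with SE = √Σ p(1 − p)/n over the four cells. With no Academy effect it rejects in about 5% of trials, whatever the selection.

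The race split of the controls is not reported and is assumed even. The calculation uses the four largest race/ethnic groups, so it omits the Native American and Pacific Islander students. Cells (Academy URM, Academy non-URM, control URM, control non-URM) are 48, 48, 52, 52 in Academy I; 30, 28, 30, 31 in Academy II; and 78, 76, 82, 83 pooled. Assumed rates are 25% URM and 50% non-URM in controls, and 50% in both groups of the Academy arm, which closes the gap completely.

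Pooled: SE = √(0.25/78 + 0.25/76 + 0.1875/82 + 0.25/83) = 0.109. The interaction detectable with 80% power (two-sided 0.05) is 2.80 × 0.109 = 0.30.

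| | SE | Detectable with 80% power | Power to detect closing a 25-point gap |
|---|---|---|---|
| Academy I | 0.137 | 38 points | 45% |
| Academy II | 0.178 | 50 points | 29% |
| Pooled | 0.109 | 30 points | 63% |

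**The case against.** The strongest defence is that no formal historical test is planned. The sentence is a narrative hypothesis without a threshold or decision rule, and every comparison the article actually describes is concurrent. The section on activities between meetings plans an Academy-versus-control comparison, Data collection plans to compare the curricula vitae of both arms, and the Discussion speaks of experimental and control students. This stands in part: the control arm is not ignored. But the comparator in the stated hypothesis remains the past, and that is the claim a reader would hold the results against.

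A reader might infer that the hypothesis would be confirmed almost certainly, whatever the Academy does. The documents do not support that without qualification. It follows on the share reading against 4%. The text also speaks of likelihood and of a rate for URM students, which can equally mean within-group rates, and then the answer depends on an unknown degree of selection.

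A reader might also infer that the analysis plan tests main effects only and excludes the interaction. The listed contrasts are examples of populations, not model terms. Both factors are named, and an analysis of variance can carry their interaction. Choice of model terms is commonly left to the analysis plan, so its absence from the article is no fault.

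It can fairly be added that the first part of the hypothesis requires a higher likelihood among experimental students, which partly guards against equality achieved through a fall among non-URM students. It does so only for the arm as a whole.

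**Conclusion.** The concern holds for the comparator. With no Academy effect the historical benchmark could well be met: almost surely if the URM share of those continuing is meant (31% at a relative rate of 0.42 and 21% at 0.25, against 4% of faculty), and with a probability that selection determines if within-group rates are meant. In neither case can success be attributed to the Academy, nor does it answer the article's own question of differential impact. This conclusion about attribution needs only the documented selection by race and career interest. The probabilities rest on assumed entry rates, assumed relative rates and the illustrative 0.42.

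**What to change.** Restate the URM hypothesis: the absolute gap between URM and non-URM students in the proportion pursuing an academic career is smaller in the Academy arm than in the concurrent control arm, arising from a higher rate among URM students. Wording it as an absolute gap avoids confusion over the sign of the difference.

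Estimate it as the arm-by-URM interaction on the risk-difference scale, which the planned analyses of variance can accommodate. Report the arm effect within URM and within non-URM students, each with a confidence interval, so that a fall among non-URM students is not read as a benefit. Leave out of this contrast the four Native American students of Academy I, who were all placed in the Academy without randomisation. Keep the historical rate as background only.

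The cost is a change of wording and some reporting. Collection of the needed data is planned in both arms, though the career outcomes are not yet complete. The real downside is imprecision: even complete closure of a 25-point gap would be detected with only about 63% power in the pooled cohorts, so the interaction should be reported as an estimate with its interval, and a non-significant result should not be read as no differential effect.
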